**Methods:**

A before-after designed intervention study will be conducted in two randomly selected secondary schools- one will be selected randomly as intervention school and the another as control school. A baseline survey will be conducted among the students of both schools by a pre-tested questionnaire to attain their current status of knowledge, attitude and practices related to NCDs. Afterward, students will be enrolled in the intervention group who will meet the eligibility criteria from the intervention school. The intervention will be given through a health promotion session to a group of students, not more than 25 at a time, by trained facilitators. A post-intervention end line survey will be conducted among all the participants from both schools using the same questionnaire 3 months after the baseline survey.

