### Participant recruitment and data collection

The study will follow a fixed study design (Additional file 1). Sample size is determined based on a previous study where a mean difference of BMI was found 1.48 between intervention and non-intervention adolescent groups after 3-months of motivational interview [23]. Expecting a similar difference, calculated sample size is 274 in each group considering effect size (E) = 1.48; standard deviation (S) = 5.98; standardized effect size (E/S) = .25; significance level, α (two-sided) = 0.05; β = 1- power = 0.2, non-response rate = 5%]. A complete list of grade-ten students will be prepared after collecting their class roll and batch number from the administrative offices of the selected schools. All the students of grade-ten will be invited to participate in the study through announcement and personal contact prior to the date of data collection.

At first, a baseline survey will be conducted among the grade ten students of both schools by a pre-tested questionnaire to attain their current status of knowledge, attitude and practices related to NCDs. Then, students from the intervention school who reported at least two NCDs risk behaviors will be invited to participate in a health education session through phone call to their parents. Selected students who will present at the day of intervention will be considered having implied consent from their parents and will be enrolled in the intervention group up to the attainment of the required sample size. Enrolled students will be given intervention through health education session. Students with any kind of physical disability or limited movement will be excluded from the study. Students from the control group will receive a one-hour session on carrier guidance. Students will be kept blind about the intervention they received. After 3 months of the baseline survey, a post-intervention survey will be conducted among the participants from both intervention and control group using the same questionnaire.

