### Ethical consideration

This study protocol got ethical clearance from Institutional Review Board (IRB) of BSMMU (BSMMU/2018/5958). Written permission will be obtained from the authorities of both schools and informed written assent will be collected from every participant prior to participation. Parents or legal guardians of the selected students will be informed about the intervention over telephone and through notice on school diary. If the parents send their children on the day of intervention, it will be regarded as their implied consent [28] to let their children participate in the health education intervention. No written consent will be obtained from the guardians other than the implied consent which has been approved by the IRB, BSMMU.

All the physical measurement will be taken in a separate room maintaining privacy and confidentiality. Female volunteer medical students will measure blood pressure and anthropometric measurements of the female participants.

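### Entry to the intervention group is decided after baseline by a risk screen, attendance and a cap, with no matching rule stated for the control school

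*Protocol article*

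**What the plan says.** All grade-ten students of both schools are invited to the baseline survey. After that, the protocol article treats the two schools differently (*Participant recruitment and data collection*).

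- **Risk screen, intervention school:** "students from the intervention school who reported at least two NCDs risk behaviors will be invited to participate in a health education session".
- **Attendance, intervention school:** "Selected students who will present at the day of intervention will be considered having implied consent from their parents". *Ethical consideration* makes clear that this is a family decision: "If the parents send their children on the day of intervention, it will be regarded as their implied consent".
- **Cap, intervention school:** those present "will be enrolled in the intervention group up to the attainment of the required sample size".
- **Control school:** "Students from the control group will receive a one-hour session on carrier guidance". No risk screen, attendance condition or cap is stated.
- **Both schools:** "Students with any kind of physical disability or limited movement will be excluded from the study".
- **End line:** "a post-intervention survey will be conducted among the participants from both intervention and control group using the same questionnaire". The abstract puts it as "A post-intervention end line survey will be conducted among all the participants from both schools".

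The *Statistical analysis plan* section names paired t-tests and McNemar tests on before-after data. It also names a comparison of the two groups on knowledge, attitude and practices before and after. It does not say how invited students who did not attend are handled.

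**The concern.** Who belongs to the intervention group is settled after the school has been allocated and the baseline data collected, partly by what the family does on one day. Eligible students who were offered the session but did not come are not counted in that group. The control group is not filtered in the same way, so the two groups may differ for reasons other than the session.

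Two selection effects are involved. Attendance may go with motivation, parental engagement or regular schooling, any of which could affect later change. The two-behaviour screen picks students who look unhealthy at baseline, and some of them would look better at a second survey without any session.

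The article says that a proven intervention could be put forward for policy (*Discussion*). For that purpose the useful quantity is the effect of offering the session to eligible students, and a group made up of attenders does not estimate it.

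**Working it through.** **1. Entry rules side by side**

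| Condition | Intervention school | Control school |
|---|---|---|
| Invited to baseline survey, written assent | yes | yes |
| No physical disability or limited movement | yes | yes (worded for the whole study) |
| At least two reported risk behaviours | yes | not stated |
| Present on the session day | yes | not stated |
| Enrolment stops at required size | yes | not stated (only the target of 274 per group) |

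The first two rows match. The last three are stated for one school only.

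**2. The plan's own figure**

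Inputs from *Participant recruitment and data collection*: difference 1.48, SD 5.98, two-sided alpha 0.05, power 80%, non-response 5%.

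n per group = 2 × [5.98 × (1.960 + 0.842) / 1.48]² = 256.3, rounded up to 257. Then 257 / 0.95 = 270.5, rounded up to 271. The stated 274 is within about 1% of this, so the sample size is not in dispute. After 5% non-response, 274 × 0.95 gives about 260 analysed per group.

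**3. Size of a possible shift from attendance (assumptions, not in the article)**

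If attenders and non-attenders would differ by d SD without any session, and a fraction a of invited students attends, attenders differ from all eligible students by (1 − a) × d. With d = 0.3:

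- a = 90%: 0.1 × 0.3 = 0.03 SD
- a = 70%: 0.3 × 0.3 = 0.09 SD
- a = 50%: 0.5 × 0.3 = 0.15 SD

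A second route gives similar values. If attenders are the most motivated fraction a, and motivation correlates 0.2 with the outcome, the shift is 0.2 × φ(z) / a, where z is the cut-off. This gives about 0.04, 0.10 and 0.16 SD for 90%, 70% and 50% attendance.

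**4. What such a shift would do to a between-group test**

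With 260 per group and no true effect, the standard error is √(2/260) = 0.088 SD. The chance of a significant result is 1 − Φ(1.96 − b/0.088) + Φ(−1.96 − b/0.088) for a shift of b SD:

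- b = 0.03: about 6%
- b = 0.09: about 18%
- b = 0.15: about 40%

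The nominal rate is 5%. These figures treat students as independent and the schools as otherwise equal.

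**5. The risk screen**

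The article gives no prevalence or repeatability for the risk behaviours, so regression to the mean cannot be sized. The screen can worsen the group's end-line status relative to controls and also inflate its before-after improvement. It can therefore work against the attendance effect on one analysis and with it on another.

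**The case against.** A reader might infer that eager students are compared with an unselected control group and that the effect is therefore overstated. The documents do not support this:

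- Nothing says that attenders are more motivated. Parents are told by telephone and school diary, so attending may be the default and absence may be ordinary.
- Nothing says that the cap works first come, first served. *The intervention* section divides candidates into groups by roll number, which is administrative.
- Controls are not wholly unselected. They give assent, the disability exclusion reads as covering them, and a target of 274 applies to them too.
- The direction is open, because the risk screen can pull the other way.
- Dividing the illustrative 0.09 SD by the planned 0.25 SD, to call it 36% of the effect, would mislead. The 0.25 is a BMI effect, while the planned between-group comparison concerns knowledge, attitude and practices. The illustration also concerns a shift in level. In the paired analysis a stable level difference cancels, and only a difference in change matters.

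Further points in the plan's favour are that Additional file 1, which is not shown, may hold a control rule; that parts of the article speak of efficacy, for which a recipients-only analysis can be a legitimate target; and that the study is presented as non-randomised with one school per arm.

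These points limit what can be claimed about direction and size. They do not remove the asymmetry in the stated rules. Other parts of the article speak of effectiveness. The abstract's reference to all participants does not place non-attenders in the intervention group. An analysis plan also cannot recover end-line data that were never collected.

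**Conclusion.** The point holds as one-sided selection after allocation. Three entry conditions are stated for the intervention school and none of them for the control school. Invited eligible students who stay away are outside the intervention group, and no handling of them is stated. The between-group comparison can be biased as a result.

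Direction and size are unknown. The range of 0.03 to 0.15 SD depends wholly on the assumed 0.3 SD difference and 90% to 50% attendance, and it leaves out the risk screen. The conclusion about controls rests on the article as published. It would narrow if the additional file applies the same rule to both schools. The change should be made, because the main contrast is affected and the remedy is cheap.

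**What to change.** 1. Before any session, define both groups from baseline data by the same rule: the same risk-behaviour criterion and the same exclusions in both schools. If a cap is needed, apply it in both schools at this stage, independently of attendance.
2. Survey all of these students at end line whether or not they attended, on the assent basis already used for the surveys. First confirm with the IRB that non-attenders may be followed, since attendance is the only parental consent the article describes, and respect any refusal.
3. Make the main comparison by school among all of these students, adjusted for the baseline value of the outcome.
4. Report the number invited and the number attending, and give the attenders-only result as secondary.

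**Cost:** some extra end-line questionnaires from students already surveyed at baseline, an IRB query, and an estimate diluted by non-attendance. If the screen is applied to controls, fewer of them may qualify. The limitation of one school per arm remains.

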### Data collection tool

A self-administered questionnaire is being constructed after reviewing several survey questionnaires in this field including Global School Health surveys [24], STEPs Survey of NCD risk factors [25], a Mongolian survey questionnaire [26] etc. The questionnaire is being constructed first in English, then translated into Bangla and again back translated into English by experts to ensure the translation. Then the questionnaire will be pre-tested among a similar population and modification of the questionnaire will be done accordingly. Finalized questionnaire (Additional file 2) will be used both in pre-intervention baseline and post-intervention end line survey.

There will be four sections in the questionnaire- the first section of the questionnaire will contain questions on socio-demographic information of the participants. The second section will contain questions about knowledge, attitudes and practice related to NCDs e.g. cardiovascular diseases, stroke, diabetes, hypertension, cervical cancer, etc. Third section will cover questions on knowledge, attitudes, perceived barriers and practice related to behavioral risk factors of NCDs e.g. diet, physical activity, smoking and alcohol, and the fourth section will hold physical measurement of the respondents such as height, weight, blood pressure, pulse, waist and hip circumference etc.

### Outcome variables

Following outcome variables will be measured.

### Knowledge

Knowledge about NCDs and risk behaviors will be measured by 25 knowledge measuring questions scoring 54 in total. Answer to the questions will be regarded as correct or incorrect based on information from standard medical textbooks and guidelines.

### Attitude

Attitude towards NCDs and its risk factors will be measured by nine attitude measuring questions in a Likert Scale.

### Practice

Practice questions will be used to evaluate dietary habit, physical activity, smoking, alcohol and substance abuse.

Based on WHO recommendations and standard practices for adolescent age, the following practices will be measured in this study.Dietary habit: presence of at least two of the following four habits will be accounted as having dietary risk behaviori.*Inadequate fruit consumption:* Less than five servings of fruits per dayii.*Inadequate vegetable consumption:* Less than five servings of vegetables per dayiii.*Excessive salt consumption:* Taking extra or raw salt during every mealiv.*Sugar Sweetened Beverage (SSB) consumption:* Consuming SSB more than 3 days per weekPhysical activity*:* Not meeting 60 min physical activity of moderate intensity per day will be regarded as physically inactive.Smoking and alcohol: Smoking regularly in the last 30 days or exposing to passive smoking more than 3 days per week will be accounted as in risk of smoking. Any amount of alcohol intake or any substance abuse in the last 30 days will be regarded as at risk.

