### Statistical analysis plan

Descriptive analysis: Socio-demographic data of the participants e.g. gender, parental occupation, parental education status, family history of NCDs, family living standard will be obtained for both intervention and control school. All categorical variables will be summarized in frequency and percentages and continuous variables in mean and standard deviation. To estimate the association of these characteristics of intervention and control group, t-tests and chi-square tests will be done.

Inferential analysis: To estimate the efficacy of the intervention, before-after data will be analyzed and paired t-test and McNemar’s chi-square tests will be done in this regard. Also, comparison will be done between the intervention and control group for pre and post-intervention status of knowledge, attitude and practices.

Association analysis: Binary regression analysis will be done to estimate the association between socio-demographic variables with changes in the outcome variables- knowledge, attitude, and practice for both groups. Also, to estimate the association of knowledge score and attitude with the change in self-reported practices, regression analysis will be done.

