### The intervention

Potential candidates for intervention will be divided into several groups based on their roll numbers. Each group will contain no more than 25 students. Then the intervention will be delivered to each group through health promotion sessions.

The intervention has been developed with the help of a psychologist, a nutritionist, a child health specialist and some public health specialists having experiences to work with adolescent health. Content of the intervention will be further improved and customized after baseline survey addressing the barriers to healthy behaviors among the target population.

The conceptual framework of the expected change through this intervention is as follows:

Intervention will be given on the following issues:

Issue 1: DietUnderstanding that there is an effect of every food we eat on our body and health besides alleviating our appetiteDemonstrating all the foods we eat every day and grouping them according to their nutritional valuesUnderstanding the metabolism and function of different food groups- carbohydrate, protein, fruits and vegetables, fries and fast food, soft and energy drinksUnderstanding and identifying healthy and unhealthy food options depending on its functionUnderstanding and identifying the link between unhealthy food options and NCDsRaising curiosity on what should be the food options to prevent NCDs

Issue 2: Physical activityDemonstrating the concept of physical activity and sedentary behaviorUnderstanding and identifying the link between physical inactivity and NCDsUnderstanding the benefits of three types of exercise (i.e., aerobic, strength building and stretching)Raising curiosity on how much and what type of physical activity should an adolescent do to prevent NCDs

Issue 3: ObesityDemonstrating the concept of normal weight and obesityEnabling to calculate one’s Body Mass Index (BMI) statusUnderstanding and identifying the potential causes of obesityUnderstanding the health consequence of childhood obesityRaising curiosity on what should be the ideal weight to stay fit and how to achieve it

Issue 4: SmokingUnderstanding the concept and the effect of active and passive smokingUnderstanding the relation of smoking with NCDsIdentifying the common reasons to start smoking at adolescent ageRaising curiosity on how to avoid starting smoking or how to quit smoking or how to reduce passive smoking

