**Table Taba:** 

Concept	Objectives	Illustration with example
Creation of motivational environment	✓ Creating a collaborative environment that evoke motivation. ✓ Giving honour to students’ autonomy and self-direction.	• Facilitators will be trained to be supportive, suspend an authoritarian role, explore capacity of the students rather than incapacity. e.g. facilitators will invite the participants to correlate different types of foods with different health status in pictorial view. Here facilitators will show a sincere interest in the students’ experiences and perspectives.
Establish rapport and express empathy	Explaining the aim of the session. Showing concern about their health. Making positive environment where the students feel free to talk about themselves.	Facilitators will ask the students to talk about their general perception regarding some common NCDs and their risk factors. Facilitators will also invite them to share their experience with NCD patients in their family. These conversations will be non-judgmental and with proper empathy.
Self-exploration of behavior	Letting students explore their experience, knowledge and ambivalence in a supportive and facilitative atmosphere.	• Facilitators will practice making open ended relevant questions, avoiding uncomfortable ones, e.g. facilitators will ask students about eating vegetables regularly. Facilitators may ask them why they eat vegetables every day or why not, and what will be the perceived health consequences in both cases without making any judgement. The co-facilitator will jot the answers briefly down a flip paper. Then, facilitators will summarize responses and give affirmation.
Practical knowledge sharing	Learning by observation.	Facilitators will show the link between sugar sweetened beverages and obesity, using pictures and short videos. Facilitators will show the consequences of different NCDs such as diabetes through videos.
Developing discrepancy	Understanding the difference between current behavior and its consequences with the desired health status	Facilitators will recapitulate their current salty food consumption and help them recognizing the discrepancy between their current behavior and their desire to stay free from cardiovascular diseases.

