Setting up self-regulatory ways	Constructing own goal and self-monitoring ways to achieve the goal	Facilitators will encourage and support students to build personal goal to consume at least five servings of fruits per day and to set self-monitoring ways to achieve the goal.

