Once the students are motivated enough to show their interest in healthy behavior, the process of negotiating change and strengthening commitment will be started by providing information. The information will be delivered in a structured way based on the principles of Bandura’s Social Cognitive Theory (SCT) [12]. The objective is to improve psychological determinants of behavior through observational learning. This intervention will emphasize supporting self-efficacy that is the belief in performance which brings the desire change [13]. As for example, if self-efficacy of a student about healthy diet is high, it means he believes that he can manage healthy eating at any situation. In this intervention, focus will be given on improving this self-efficacy through sharing experience, modeling and through verbal persuasion using some trend words, like “you are Bangladesh, you can do it”. In addition, education about NCDs and its risk factors will be given in such a way that allows them to reflect, letting them develop, and evaluate their own outcome expectancy which is, another behavior changing component of Bandura’s theory [18].

This intervention is not aimed to bring any environmental change. Yet, this intervention will demonstrate choices and make them skilled, thus empower them to pick the most suitable choice for themselves. As for example, they will be taught with a range of free hand exercises by role modeling and by making some role models among themselves. Now as they are mastered on several exercises, they can do any of them at their convenience, to acquire the daily physical activity recommendation. Leaflets on healthy diet, physical activity and anti-tobacco message will be provided to take home, which is expected to improve the social support to some extent. These will eventually improve their self-efficacy and self-regulatory capacity and thus influence health behavior.

An intervention is judged by its cost-effectiveness when referring for mass population. Meta-analysis on this issue found that group intervention is the least expensive yet most cost-effective interventional way among the adolescents [37]. This proposed intervention is designed for group and therefore, is more realistic in the low socio-economic context like Bangladesh to deliver the intervention to utilize the limited resources best. Thus, upon its effectiveness being proven, this intervention can be advocated to policies.

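### The yes/no diet and smoking composites can hide changes in the separate habits the intervention targets, so those habits should be analysed as outcomes in their own right

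*Protocol article*

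**What the plan says.** **Diet (Outcome variables, Practice).** Four habits are each given a cut-off: fewer than five fruit servings a day, fewer than five vegetable servings a day, extra or raw salt at every meal, and sweetened drinks on more than 3 days a week. They are then combined: "presence of at least two of the following four habits will be accounted as having dietary risk" behavior.

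**Smoking (same section).** "Smoking regularly in the last 30 days or exposing to passive smoking more than 3 days per week will be accounted as in risk". Own smoking and exposure to others' smoke share one code.

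**What the session targets (The intervention, and its table of the sequential framework).** The pieces are addressed one by one. Students are helped to "build personal goal to consume at least five servings of fruits per day". For drinks, "Facilitators will show the link between sugar sweetened beverages and obesity". The table also takes up the students' salty food consumption. Issue 4 covers "how to quit smoking or how to reduce passive smoking".

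**Analysis (Statistical analysis plan).** Efficacy is tested before and after by paired t-test and McNemar's test, and the groups are also compared before and after the intervention. Separately, under association analysis: "Binary regression analysis will be done to estimate the association between socio-demographic variables with changes in the outcome variables", namely knowledge, attitude and practice. Knowledge is a 54-point score and attitude is nine Likert items.

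**The concern.** The general objective is to reduce behavioural risk factors, and the diet and smoking codes are how that is read for those two domains. Each code turns several targeted behaviours into one yes/no item. A student can improve on something the session taught and keep the same code.

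McNemar's test uses only students whose code changes between surveys, so such a student contributes nothing. If this pattern is common, a useful effect on sweetened drinks, salt or quitting could be missed in the composite even where it would be plain in the component. The article defines each habit individually but does not commit to analysing them individually.

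A smaller related point is that binary regression on changes in the knowledge and attitude scores requires a yes/no cut of a change score, and no cut is stated.

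**Working it through.** **The plan's own figure.** The sample size rests on BMI, with difference 1.48, SD 5.98, two-sided alpha 0.05 and power 0.80. n = 2 × [5.98 × (1.960 + 0.842) / 1.48]² gives 257 per group, and 257 / 0.95 = 271. The t-based version gives 258, then 272. Both are within 3% of the stated 274, so the figure reproduces. BMI is continuous, so the coding does not affect it. Below I use 274 × 0.95 ≈ 260 per group.

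**Diet: which improvements the rule can see.** Four yes/no habits give 16 patterns, of which 6 + 4 + 1 = 11 are at risk (two, three or four habits).
- Dropping exactly one habit: 6×2 = 12 ways from two habits, all of which register. There are 4×3 = 12 ways from three habits and 4 from four habits, none of which registers. So 12 of 28 register and 16 of 28 (57%) do not.
- Dropping one or more habits: 18 of 18 register from two habits, 16 of 28 from three and 5 of 15 from four. So 39 of 61 (64%) register and 22 (36%) do not.

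These are counts of patterns, not of students. Two cases matter most. A student short on both fruit and vegetables who stops raw salt and sweetened drinks still has two habits. A student with all four habits who fully meets the fruit goal still has three.

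Movement below a cut-off is also invisible, for example from 1 to 4 fruit servings. If servings were Poisson (assumption), doubling the mean from 1 to 2 would move the share below five only from 99.6% to 94.7%.

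**Diet: what this does to power.** The article gives no baseline rates, so all of these are assumptions: the four habits are independent, fruit and vegetable inadequacy each equal f and do not change, salt s falls from 30% to 15%, and sweetened drinks b fall from 40% to 20%.

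P(at risk) = f² + 2f(1−f)[1 − (1−s)(1−b)] + (1−f)²sb

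At f = 0.90:
- Before: 0.81 + 0.18 × 0.58 + 0.01 × 0.12 = 0.916.
- After: 0.81 + 0.18 × 0.32 + 0.01 × 0.03 = 0.868.

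Power is for a two-sided comparison of two independent proportions at 260 per group: Φ[(d − 1.96·se₀)/se₁], with se₀ pooled and se₁ unpooled.

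| Outcome | Unchanged | Both habits halved | Drop (points) | Power |
|---|---|---|---|---|
| Composite, f = 60% | 65.8% | 51.8% | 13.9 | 0.90 |
| Composite, f = 80% | 83.0% | 74.4% | 8.7 | 0.68 |
| Composite, f = 90% | 91.6% | 86.8% | 4.8 | 0.42 |
| Composite, f = 95% | 95.8% | 93.3% | 2.5 | 0.24 |
| Salt alone | 30% | 15% | 15 | 0.985 |
| Sweetened drinks alone | 40% | 20% | 20 | 0.999 |

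This is a between-group calculation that ignores clustering by school. It serves to compare composite with component, not to give the trial's actual power.

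**Smoking.** Let active smoking be a and passive exposure e, independent of each other (assumption). At risk = 1 − (1−a)(1−e). Of the students who quit, the share whose code changes is 1 − e, that is 70%, 50% or 30% when e is 30, 50 or 70%. For example, with a = 10% halved and e = 50%, active smoking falls 5 points while the composite falls from 55.0% to 52.5%, or 2.5 points.

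**Scores.** The paired t-test can use the full score change, so the efficacy analysis of knowledge and attitude need lose nothing. Only the association analysis calls for a yes/no change. Its loss cannot be computed without a cut-point, and a cut at any increase would still register every gain.

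**The case against.** The other side has real points.

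- **The habits are already defined one by one.** Nothing says the composite replaces them, and McNemar's test is not confined to composites. This stands as far as it goes, and it is why the remedy is cheap. But the article states the combining rule and makes no commitment to the components.
- **The fruit cut-off is the session's own goal.** Testing whether students reach the taught target is defensible. That supports keeping fruit as its own yes/no outcome. It does not support merging it with three other habits.
- **Passive exposure is part of the intervention.** A reader might infer from "This intervention is not aimed to bring any environmental change" in the Discussion that exposure to others' smoke lies outside what the session tries to change. The documents do not support that. Issue 4 teaches how to reduce it, and the take-home leaflets are expected to improve social support to some extent. The surviving point is that two distinct targets share one code, which hides which of them moved. Small absolute changes in the smoking composite would also partly reflect low active smoking, not only the merging.
- **Knowledge and attitude.** A reader might take binary regression to weaken the efficacy test of the scores. It does not, because it appears only in the association analysis.
- **More outcomes mean more tests.** True, and it should be handled by naming them as secondary.

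**Conclusion.** The point holds for the diet and smoking codes. As written, they cannot register some changes the session aims at, and McNemar's test on the composites would ignore those students. The logic needs no assumption, but the size does. In the scenario above, the composite's power runs from 0.90 at 60% fruit and vegetable inadequacy to 0.24 at 95%, while the single habits keep 0.985 or more. Independence and every prevalence are assumed.

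Two stronger readings are not supported. One is that these outcomes are already near a ceiling. The Abstract calls unhealthy dietary habit common, and enrolling intervention students with at least two risk behaviours may concentrate them, but no rate is given. The other is that a null result could not be interpreted. Many improvements do register (12 of 28 single-habit drops, 39 of 61 improvements overall), and knowledge, attitude, physical activity, blood pressure, BMI and waist and hip circumference are measured separately.

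This is a worthwhile gain in sensitivity and clarity, not a fatal flaw.

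**What to change.** 1. State that each of the four diet habits will be analysed as a separate outcome. A 0–4 habit count, or servings per day and days per week, can be used instead if the questionnaire records them (it is not shown here).
2. Report active smoking and passive exposure as two outcomes.
3. Keep the at-least-two diet code and the combined smoking code as descriptive summaries.
4. In the association analysis only, replace binary regression of change in the knowledge and attitude scores with linear regression of the end-line score on the baseline score and the socio-demographic covariates. The paired t-test of scores needs no change on this account.

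**Cost.** The change is to analysis wording. Habit-level analysis needs no new data, because the cut-offs are already defined. The price is a few more outcomes and tests, which should be listed in advance as secondary.
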